# Objectives

## Primary objective

The primary objective of the study is to assess the efficacy of RTS,S/AS02A candidate malaria vaccine against clinical episodes of *P. falciparum* malaria in children aged 1 to 4 years at first vaccination, over a 6 month surveillance period starting 14 days after dose 3 (day 74), in Cohort 1.

See Section 10.2 for delineation of primary endpoint and Section 10.1 for delineation of clinical case definitions.

## Secondary objectives

The secondary objectives correspond exclusively to data collected and endpoints during the double-blind phase of the study (months 0 to 8½). See Section 10.1 for delineation of clinical case definitions.

### Cohort 1

***Efficacy***

To assess, in children (1 to 4 years at first vaccination) the efficacy of RTS,S/AS02A candidate malaria vaccine against:

- clinical episodes of *P. falciparum* malaria of differing severity over a 6 month surveillance period starting 14 days after dose 3 (day 74).
- anaemia presenting clinically over a 6 month surveillance period starting 14 days after dose 3 (day 74) or detected at cross-sectional survey at 6½ months after dose 3 (month 8½).
- asexual falciparum parasitaemia (prevalence and density) at 6½ months after dose 3 (month 8½).

***Safety***

To assess in children (1 to 4 years of age at first vaccination):

- safety of RTS,S/AS02A malaria vaccine until 6½ months after dose 3 (month 8½).
- reactogenicity of RTS,S/AS02A malaria vaccine from the time of first vaccination until one month after dose 3 (day 90).

***Immunogenicity***

- To assess the humoral immune response to the circumsporozoite protein (CS) antigen of the RTS,S/AS02A malaria candidate vaccine in children (1 to 4 years of age at first vaccination).

See Section 10.3.1 for delineation of secondary endpoints corresponding to Cohort 1.

### Cohort 2

***Efficacy***

- To assess in children (1 to 4 years of age at first vaccination) the efficacy of RTS, S/AS02A malaria candidate vaccine in delaying time to first asexual falciparum infection.

***Safety***

To assess in children (1 to 4 years of age at first vaccination):

- safety of RTS,S/AS02A malaria vaccine until 6½ months after dose 3 (month 8½).
- reactogenicity of RTS,S/AS02A malaria vaccine from the time of first vaccination until one month after dose 3 (day 90).

***Immunogenicity***

To assess in children (1 to 4 years of age at first vaccination), the humoral immune response to:

- the HBs antigen of the RTS,S/AS02A malaria candidate vaccine.
- the CS antigen of the RTS,S/AS02A malaria candidate vaccine.

See Section 10.3.2 for delineation of secondary endpoints corresponding to Cohort 2.

## Tertiary objectives

All the tertiary objectives correspond to endpoints and data collected during the single-blind phase of the study (months 8½ to 21). See Section 10.1 for delineation of clinical case definitions.

### Cohort 1

***Efficacy***

To assess in children (1 to 4 years of age at first vaccination) the efficacy of RTS,S/AS02A candidate malaria vaccine against:

- clinical episodes of *P. falciparum* malaria of differing severity over the surveillance period.
- anaemia presenting clinically over the surveillance period or detected at cross-sectional survey at 19 months after dose 3 (month 21).
- asexual *P. falciparum* parasitaemia (prevalence and density) at 19 months post dose 3 (month 21).

***Safety***

- To assess in children (1 to 4 years of age at first vaccination) the safety of the RTS,S/AS02A malaria candidate vaccine during months 8½ to 21.

***Immunogenicity***

- To assess the humoral immune response to the CS antigen of the RTS,S/AS02A malaria candidate vaccine at 19 months post dose 3 (month 21) in children (1 to 4 years of age at first vaccination).

See Section 10.4.1 for delineation of tertiary endpoints for Cohort 1.

### Cohort 2

***Safety***

- To assess in children (1 to 4 years of age at first vaccination) the safety of the RTS,S/AS02A malaria candidate vaccine during months 8½ to 21.

***Immunogenicity***

To assess in children (1 to 4 years of age at first vaccination) the humoral immune response to:

- the CS antigen of the RTS,S/AS02A malaria candidate vaccine at 19 months post dose 3 (month 21).
- the HBs antigen of the RTS,S/AS02A malaria candidate vaccine at 19 months post dose 3 (month 21).

See Section 10.4.2 for delineation of tertiary endpoints for Cohort 2.

# Study Design Overview

**(Amended January 17, 2003)**

- Phase IIb study in one centre and two study sites (towns of Manhiça and Ilha Josina).
- The necessary number of healthy male and female children aged 1 to 4 years (inclusive) will be screened in order to enrol ***1980*** ~~1920~~ subjects in the study.
  **(Amended January 17, 2003)**
- Duration per subject: approximately 24 months.
- Screening will be performed within ***90*** ~~35~~ days.
  **(Amended January 17, 2003)**
- Enrolment will be performed within 12 weeks.
- Controlled:
- 3 doses of hepatitis B vaccine (Engerix‑B™) to children of ***24*** ~~18~~ months and older.
- 2 doses of a 7-valent pneumococcal conjugate vaccine (Prevnar®, Wyeth Lederle Vaccines) at first and third vaccination and 1 dose of Haemophilus influenzae type b vaccine (Hiberix™) at second vaccination to children less than ***24*** ~~18~~ months. **(Amended January 17, 2003)**
- 3 doses of vaccine (RTS,S/AS02A or control) will be administered using a 0, 1 and 2 month vaccination schedule.
  A full dose (0.5 ml) of the control vaccine or a paediatric dose (0.25 ml dose volume) of the RTS,S/AS02A vaccine will be administered at each vaccination.
- Blinding:
- Vaccination and surveillance period (double-blind phase) from month 0 to the data lock point for primary and secondary objectives (month 8½).
- Single-blind surveillance period (study subjects will remain blinded to treatment allocation until study end as will study staff responsible for endpoint evaluation at health facilities and at cross-sectional surveys) from month 8½ to data lock point for analysis of tertiary objectives (month 21).
- Subjects will be randomly assigned in a 1:1 fashion to receive either the RTS,S/AS02A candidate malaria vaccine or one of the control vaccine regimes. See Section 6.4 for a detailed description of the randomization method.
- Two cohorts will evaluate the effect of the malaria candidate vaccine on clinical malaria disease and malaria infection (Cohorts 1 and 2 respectively, with 1564 subjects in Cohort 1 and ***416*** ~~356~~ subjects in Cohort 2). In Cohort 2 where the efficacy of the vaccine against infection will be evaluated, subjects will receive 4 weeks prior to onset of surveillance one dose of sulfadoxine-pyrimethamine and amodiaquine per day for 3 days, so as to clear any parasitaemia. **(Amended January 17, 2003)**
- Self-contained study, i.e. this study will be independent of other studies.
- Data collection will be by electronic remote data entry (RDE)

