### Surveillance for malaria infection (Cohort 2)

Four weeks prior to the start of surveillance for malaria infection (i.e. 2 weeks before the third vaccination), asymptomatic parasitaemia will be cleared in children enrolled into Cohort 2 with amodiaquine-SP (sulfadoxine and pyrimethamine : 25 mg/kg body weight p.o. and 1.25 mg/kg body weight p.o. single dose; amodiaquine: 10 mg/kg body weight p.o. once daily for three days). The prevalence of asymptomatic parasitaemia in the study area is high, therefore all children will receive a drug for clearance of malaria parasites without prior blood sampling to determine parasitaemia. The first dose of amodiaquine-SP will be administered at a field worker visit 2 weeks before the third dose of vaccine (day 46). The absence of parasitaemia will be checked by taking blood for a blood slide at clinic visit 4 (day 60). Any child with any level of parasitaemia at this point will be treated with a second-line treatment for malaria and will not undergo the surveillance period for active detection of infection. All such children will not contribute to the endpoint for vaccine efficacy in Cohort 2.

The surveillance period for malaria infection will begin 14 days after the third dose of vaccine (day 74). Surveillance will continue with the clinic visit on day 90 and then field worker visits every two weeks (one visit every 14 days) for the following 2½ months (six visits) and then monthly for 2 months (two visits at months 7 and 8), and ending with the clinic visit at month 8½. Blood samples will be taken for examination of malaria parasitaemia and parasite genotyping at each visit. The first blood slide examination will be made on the first day of surveillance, i.e. 14 days after the third dose (day 74). At first detection of malaria infection with asexual forms of *P. falciparum* in a child, either by field worker surveillance or on clinical presentation with malaria disease at a health facility,the child will be considered to have met the endpoint for vaccine efficacy in Cohort 2 and no further visits for surveillance of infection will be undertaken. The child will still be under morbidity surveillance and will receive monthly visits by field workers for SAE surveillance and will also take part in cross-sectional surveys at month 8½ and month 21.

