### Management and treatment of malaria in all subjects

Children presenting with uncomplicated malaria not requiring parental treatment will receive treatment with combination therapy of amodiaquine and sulfadoxine-pyrimethamine (SP) under supervision at the health care facility and will be managed according to standard medical practice.

The dosage of amodiaquine-SP to be used will be:

- single dose of sulfadoxine (25 mg/kg body weight p.o.) and pyrimethamine (1.25 mg/kg body weight p.o.)
- amodiaquine: 10 mg/kg body weight p.o. once daily for three days.

All dosages will be rounded to the nearest quarter tablet.

All children requiring parenteral treatment or with complicated malaria will be admitted to Manhiça Hospital and will receive quinine. Full details of malaria case management are contained in an SOP at the investigator’s site.

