| · | | Recording of axillary body temperature and any local or general solicited symptoms experienced at time of field worker visit, and within the previous 24 hours, onto diary cards by field workers, on the 3 subsequent days after vaccination. |
| ***Field worker visit 7: for Active Detection of Infection (14 days pre dose 3)*** | | |
| ***Day 46:*** | | |
| · | Treatment of all subjects with antimalarial (administration of first dose of amodiaquine and SP and provision of following two doses) without checking for parasitaemia | |
| · | | Reporting of any Serious Adverse Events (SAEs) which the vaccinee has experienced since last visit. |
| **Clinic Visit 4: Third vaccination (27 to 37 days after Visit 3)** | | |
| **Day 60: Post vaccination 2** | | |
| · | Verification of photo ID and subject number | |
| · | The investigator must record all non-serious adverse events that occur 1 month (minimum 30 days) post-vaccination 2. | |
| · | Reporting of any Serious Adverse Events (SAEs) which the vaccinee has experienced since the previous vaccine dose. | |
| · | Physical examination –pre-vaccination axillary body temperature . | |
| · | Checking of elimination criteria and contraindications to vaccination. | |
| · | Recording of concomitant medication. | |
| · | Finger prick blood sample collected (0.5-1 ml) for:   - Blood film for parasitaemia determination - ***Parasite genotyping***   **(Amended January 17, 2003)** | |
| · | Intra-muscular (IM) administration of the third vaccine dose in the deltoid region of the left arm. | |
| · | Each vaccinee will be closely observed for one hour or longer if necessary with appropriate medical treatment readily available in case of a rare anaphylactic reaction following the administration of the vaccine. After the observation period, axillary body temperature will be retaken, and together with local and general signs and symptoms that may occur, will be recorded in the CRF by the investigator. | |
| ***Field worker vaccination follow-up visits 7-9 after third vaccination*** | | |
| ***Days 61, 62 and 63:*** | | |
| · | Recording of concomitant medication. | |
| · | | Reporting of any Serious Adverse Events (SAEs) which the vaccinee has experienced since last visit. |
| · | | Recording of axillary body temperature and any local or general solicited symptoms experienced at time of field worker visit, and within the previous 24 hours, onto diary cards by field workers, on the 3 subsequent days after vaccination. |

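### The day-46 parasite-clearance regimen for Cohort 2 is stated inconsistently: SP daily for three days in the overview, SP once in section 5.2.7

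*Supplement*

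**What the plan says.** The clearance procedure for Cohort 2 appears in four places in the current protocol text.

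- **Synopsis (study design) and section 3, Study Design Overview.** The same sentence in both: four weeks before surveillance, subjects receive "one dose of sulfadoxine-pyrimethamine and amodiaquine per day for 3 days, so as to clear any parasitaemia". No amount per kg is given.
- **Section 5.2.7, Surveillance for malaria infection (Cohort 2).** The same procedure at the same time, with amounts. Sulfadoxine and pyrimethamine are given as "25 mg/kg body weight p.o. and 1.25 mg/kg body weight p.o. single dose"; the other drug is "amodiaquine: 10 mg/kg body weight p.o. once daily for three days". All children are treated without a blood test first. A slide is taken on day 60, and any child still positive leaves the infection endpoint.
- **Section 5.6, field worker visit on day 46.** The instruction is "administration of first dose of amodiaquine and SP and provision of following two doses".

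Section 10.7.2.1 adds that a child treated for malaria counts as not susceptible for 28 days, and that this time is deducted from the time at risk.

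**The concern.** A protocol should give one answer to the question of how many times each drug is given. Here the overview sentence, read plainly, says three times for SP, and section 5.2.7 says once. The instruction that the field worker would follow does not settle it, because it does not say what the two doses left behind consist of.

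The stake is chiefly safety and uniform handling. The regimen is dosed by weight and given to healthy children aged 1 to 4, none of them tested beforehand. The first dose is given by a field worker and the rest is left with the family. Section 5.5 schedules no study visit between day 46 and day 60, so the unclear part of the regimen is also the unobserved part.

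The procedure also defines the parasite-free starting point for the Cohort 2 infection endpoint, so its description should be unambiguous for that reason too.

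**Working it through.** The plan states no derived figure on this point. The check is a comparison of the passages, followed by simple arithmetic.

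**Do the passages describe the same procedure?** Yes. The overview places it four weeks before surveillance. Section 5.2.7 places it on day 46, with surveillance starting on day 74: 74 − 46 = 28 days. Section 5.6 also gives day 46.

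**Number of administrations**

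| Place | SP | Amodiaquine |
|---|---|---|
| Synopsis and section 3, plain reading | 3 | 3 |
| Section 5.2.7 | 1 | 3 |
| Section 5.6, day 46 | 1 given; not stated for the two left at home | 1 given, 2 left at home if both contain amodiaquine |

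**Total amount.** The only amounts given for clearance are in section 5.2.7: 25 mg/kg sulfadoxine, 1.25 mg/kg pyrimethamine and 10 mg/kg amodiaquine per dose. The overview gives none, so its totals rest on the assumption that each daily SP dose equals the dose in 5.2.7. Total = number of doses × amount per dose.

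- Sulfadoxine: 3 × 25 = 75 mg/kg against 1 × 25 = 25 mg/kg, ratio 3.
- Pyrimethamine: 3 × 1.25 = 3.75 mg/kg against 1 × 1.25 = 1.25 mg/kg, ratio 3.
- Amodiaquine: 3 × 10 = 30 mg/kg under both, ratio 1.

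The count of 3 against 1 comes directly from the text. The figure of 75 mg/kg does not appear in the documents and holds only under the stated assumption.

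**Timing.** Day 46 to the day-60 slide is 60 − 46 = 14 days. Day 46 to the start of surveillance is 28 days, the same length as the non-susceptible period in section 10.7.2.1. If doses are given on consecutive days, a three-day course ends on day 46 + 2 = day 48, and 74 − 48 = 26 days. The last SP dose would then fall 28 days before surveillance if SP is given once, and 26 days before if it is given three times. Section 10.7.2.1 does not say whether its 28 days run from the first or the last dose, and it is written for treatment of malaria, not for clearance. This is a point to check once the regimen is settled, not an error already shown.

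**The case against.** The best defence is that only section 5.2.7 gives a usable dose. The overview sentence is a compressed summary with no amounts, and no child could be dosed from it alone. It can also be parsed as one dose of SP, plus amodiaquine each day for three days, which would agree with 5.2.7. This has some force. But it is not the plain reading, and a paediatric dosing statement should not depend on a favourable one.

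A reader might infer that the day-46 instruction contradicts section 5.2.7. It does not clearly do so. Section 5.2.7 itself calls the day-46 administration the first dose of the combination while giving SP once, so the wording in 5.6 can mean day one of a course whose later doses are amodiaquine only. The instruction is ambiguous and could fit either reading.

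A reader might also set section 5.2.11 against the overview, since it too gives SP once. That section covers children who present with clinical malaria. It is a different use of the drugs and no part of this contradiction.

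Finally, one might infer that the infection endpoint is biased. The documents do not support that. Allocation is randomised and blinded, both arms undergo the same clearance at one site, and the day-60 slide removes children who remain positive. Nothing suggests that the arms would be handled differently, and any residual drug effect on early infections cannot be calculated from the documents. The primary endpoint belongs to Cohort 1 and is not touched.

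**Conclusion.** The point stands as an inconsistency in the current text. The Synopsis and section 3, read plainly, give SP on three days; section 5.2.7 gives it once; section 5.6 leaves the content of the two take-home doses open. The certain difference is three SP administrations against one. The difference of 75 against 25 mg/kg sulfadoxine is conditional on the amount per dose in 5.2.7.

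It would be wrong to speak of a threefold difference in the regimen as a whole, because amodiaquine is 30 mg/kg on either reading.

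The matter affects up to 416 planned children and is mainly one of dosing safety and consistency. No bias in the comparison of the arms is shown. The documents do not establish which regimen was intended, and none is preferred here.

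**What to change.** The clinical team should decide on one regimen and reconcile the Synopsis, section 3, section 5.2.7 and the day-46 instruction in section 5.6 to it. Ideally it is written in full once, with cross-references elsewhere.

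The day-46 instruction should state how many doses of each drug are given at the visit and how many of each are left with the family.

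Once that is settled, confirm that the interval from day 46 to day 74 is consistent with the 28-day rule in section 10.7.2.1, including the day from which the 28 days are counted.

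The cost is a protocol wording change and a check of the field-worker SOP. Sample size, visits and analysis methods are unaffected.

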# Study Site and Population

## Study site

The study will be conducted in the Manhiça District of Mozambique. Refer to Sections 1.1.3 to 1.1.7 of introduction for a detailed description of study area and the participating health facilities.

CISM is located adjacent to the District Hospital, in Manhiça the principal town of Manhiça District. CISM is connected by a tarmac road to the Ilha Josina health facility, which lies 40 km to the north of Manhiça town. Communication between the coordination centre at CISM and Ilha Josina is by means of short wave radio. Project staff including providers of clinical care, fieldworkers, laboratory staff and drivers will be resident at the two sites.

Children for Cohorts 1 and 2 will be recruited from Manhiça District, in the areas around Manhiça town and from Ilha Josina respectively. Vaccinations will be performed at both Manhiça Hospital and Ilha Josina Health Facility.

A full morbidity surveillance system for the detection of clinical cases and serious adverse events is established at Manhiça Hospital and will be established by study start at Ilha Josina Health Facility. At both sites, this will provide 24-hour provision of clinical care supervised by a clinician (doctor/medical assistant) with facilities and staff to perform blood slide examination for malaria parasites. Although at Ilha Josina Health Facility there are emergency drugs including oxygen available, there are no inpatient facilities. Children requiring inpatient care will be transferred to Manhiça Hospital by project vehicles that will be permanently stationed at Ilha Josina, to ensure 24-hour availability.

## Number of subjects

The necessary number of subjects will be screened in order to enrol ***1980*** ~~1920~~ eligible subjects; 1564 to Cohort 1 and ***416*** ~~356~~ to Cohort 2. Subjects will be recruited by non-coercive methods according to existing policies of the CISM (see Appendix C). Subjects will be male and female children of 1 to 4 years of age (up to but not including their 5th birthday) residing in the Manhiça District. See Section 6.4 for a detailed description of the criteria used in the estimation of sample size.
**(Amended January 17, 2003)**

Only subjects for whom the investigator believes the requirements of the protocol will be complied with (e.g. completion of the diary cards, return for follow-up visits) should be enrolled in the study.

## Inclusion criteria

- Healthy male and female children, 1 to 4 years of age at the time of first vaccination (up to but not including 5th birthday).
- Written/thumbprinted and witnessed informed consent obtained from the parents or legal guardians, after they have been informed of the risks and benefits of the study in a language, which they clearly understand.
- Free of obvious health problems as established by medical history and clinical examination before entering into the study.
- Availability for the duration of the immunisation and follow-up period.

## Exclusion criteria for enrolment

The following criteria should be checked at the time of study entry. If any apply at the time of study entry, the subject must not be included in the study:

- Major congenital defects or serious chronic illness. Acute or chronic, clinically significant pulmonary, cardiovascular, hepatic or renal functional abnormality, as determined by physical examination or laboratory screening tests (see below). Chronic carriers of the HBsAg will not be excluded from the clinical trial provided they are clinically asymptomatic.
- Haematocrit of less than 25%.
- History of allergic reactions to vaccination.
- History of allergic reactions to any component of the Hiberix™, Prevnar® or Engerix-B™ vaccines.
- Chronic administration (defined as more than 14 days) of immuno-suppressants or other immune modifying drugs within six months prior to the first vaccine dose (for corticosteroids, this will mean prednisone, or equivalent,  0.5 mg/kg/day. Inhaled and topical steroids are allowed.)
- Previous vaccination with an experimental vaccine.
- Previous vaccination with hepatitis B vaccine (as documented on health card) in children equal to or more than ***24*** ~~18~~ months of age. **(Amended January 17, 2003)**
- Simultaneous participation in any other clinical trial.
- Any other findings which in the opinion of the investigators would increase the risk of having an adverse outcome from participation in the trial.
- Severe malnutrition defined as weight for ***height***  -3z scores[[28]](#endnote-29).
